### Statistical power and sample size

Based on our previous research, **160** families (80 per group) will be recruited to detect a small-medium effect size (f^2^ = .10; [52]) in adherence to physical activity (primary outcome) with a type one error of .05, an average correlation of .75 across time for our DV of interest, and a power of .80. Our sample size also considers the main 2 (group) x 2 (parent/child) x 4 (time) repeated measures design using G-Power [53] and a potential 25 % attrition rate similar to the pilot study. Finally, the evaluation of physiological outcomes of participants across time will follow a 2 (condition) x 2 (time) interaction. Physiological parameters have larger effect sizes than the social/psychological variables in the study due to smaller standard error scores. The proposed sample size is, therefore, more than adequate to ensure sufficient statistical power for the physiological measurements.

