### Pilot research

This research builds on a pilot study conducted from January 2007 until December 2008 in the Capitol Region District of British Columbia that intervened with 85 families [22]. The measures, intervention protocol, recruitment, training of personnel, and related practicalities were all tested during the pilot. The pilot work was successful in demonstrating both sustained recruitment and expected outcomes. As hypothesized, the planning intervention resulted in higher family physical activity compared to the standard condition (effect size η = .08 to .11). Furthermore, the results showed no changes to intention or perceived behavioral control, supporting the concept of a self-regulatory planning phase in physical activity adherence. While these findings were promising, the study was pilot in nature and thus the current trial represents an extension of the work; increasing the methodological veracity and the sophistication of the intervention. First, this study improves upon the pilot study by using direct assessment of physical activity (i.e., accelerometry) rather than self-report, which is the recommended form of assessment for these population groups [23, 24]. Second, this study will evaluate the efficacy of the intervention across six months rather than the one-month time frame used in the pilot. Third, the current study provides a more comprehensive planning skills intervention package based on contemporary theory [20, 21]. Fourth, the study will include health-related assessments of quality of life and physical fitness which were absent in the pilot. These assessments are important markers of health benefits in addition to physical activity and help ascertain whether any changes in behavior actually link to the sought after health improvements that form the central rationale for physical activity promotion.

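### The 160 families do not follow from the printed effect size, correlation, power and attrition; the effect-size metric and the powered test need to be restated

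*Protocol article*

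**What the plan says.** In the protocol article, Statistical power and sample size sets the target at 160 families in two equal arms. In its words, these "will be recruited to detect a small-medium effect size (f^2^ = .10; [52]) in adherence to physical activity (primary outcome". Alpha is set at .05. For the other inputs the paragraph lists "an average correlation of .75 across time for our DV of interest, and a power of .80". It then states that the number also takes account of a 2 (group) x 2 (parent/child) x 4 (time) repeated-measures design run in G-Power, and of possible attrition of 25%. It does not say which effect was powered, gives no nonsphericity epsilon, and does not separate the number before attrition from the number after it.

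Analysis strategy makes the primary analysis a 2 (condition) x 4 (time) repeated-measures ANOVA on one randomly chosen child per household. Present research and the primary-outcome heading put the question at six months, as a change from baseline. Pilot research reports the earlier result as "effect size η = .08 to .11".

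**The concern.** The paragraph prints its inputs and its answer, so a reader should be able to get from one to the other. The effect size is printed as f-squared, and f-squared = .10 means f = .316, whereas f = .10 means f-squared = .01. That is a tenfold difference in the quantity that drives power. The effect being tested is also unnamed. At a correlation of .75, condition x time and the condition main effect need very different numbers, because a high correlation helps the first and hurts the second. The pilot effect, the natural cross-check, is printed in a third metric.

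At stake is whether the claim of 80% power belongs to any identifiable effect and test. Depending on what was meant, the same 160 families are far more than needed, adequate or well short.

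**Working it through.** **Inputs.** From Statistical power and sample size: f-squared = .10, alpha = .05, rho = .75, power = .80, attrition 25%, so 160 x .75 = 120 completers. From Analysis strategy: k = 2 groups, m = 4 times, one child per family. Assumed here: sphericity (epsilon = 1) unless stated otherwise, and N as total completers.

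**Formulas (noncentral F).**
- Condition main effect: lambda = f² N m / (1 + (m − 1) rho), df = k − 1 and N − k. With m = 4 and rho = .75 this is f² N x 4/3.25.
- Condition x time: lambda = f² N m epsilon / (1 − rho), df = (k − 1)(m − 1) epsilon and (N − k)(m − 1) epsilon. With epsilon = 1 this is f² N x 16.
- Families to recruit = N / .75, rounded up.

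**Attempt to reproduce 160 for the 2 x 4 design.**

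| Effect size | Test | Completers for 80% | Families | Power with 120 completers |
|---|---|---|---|---|
| f² = .10 | condition x time | 9 | 12 | > 99.9% |
| f² = .10 | condition main effect | 66 | 88 | 97% |
| f = .10 | condition x time | 70 | 94 | 97% |
| f = .10 | condition main effect | 640 | 854 | 23% |

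With equal arms the first row becomes 10 completers and 14 families.

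**2 x 2 x 4 variants, f² = .10.**
- Parent/child as a second between factor (four cells): 14 completers and 19 families for cells x time; 93 and 124 between cells (94 and 126 with equal arms).
- Parent/child as repeated measures (m = 8): 6 and 8 for condition x time; 64 and 86 for the main effect.

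**2 x 2 x 4 variants, f = .10.** Four cells: 101 and 135, or 890 and 1,187. Eight measures: 46 and 62, or 616 and 822.

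No row gives 160.

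**What comes close to 160.**
- f = .10 with an unstated epsilon: four cells x time at epsilon = .77 needs 120 completers and 160 families; two groups x time at epsilon = .45 needs 121 and 162.
- Dropping the correlation: a four-cell omnibus test at f² = .10 with lambda = f²(N − 4) needs 117 (156 families), or 120 in equal cells (160 families).
- Dropping both the effect size and the correlation: a difference of .5 SD needs 64 per arm, and 64 x 1.25 = 80 per arm.

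Each needs an input that the paragraph does not state, or omits one that it does.

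**Pilot effect.** f² = eta² / (1 − eta²).
- Literal eta: .08² / (1 − .08²) = .0064 and .11² / (1 − .11²) = .0122, which is 16 to 8 times below .10.
- If the values are eta-squared: .08/.92 = .087 and .11/.89 = .124, which bracket .10.

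**The two metrics in SD units.** If the arms differ by (0, d, d, d) at the four times, the interaction f = d x √(3/64) = .2165 d. Then f = .316 is d = 1.46 SD and f = .10 is d = .46 SD.

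**What 120 completers can detect at 80% power.** At rho = .75 and epsilon = 1: f of about .076 for condition x time, or about .23 for the condition main effect. For a six-month difference adjusted for baseline with 60 per arm, d ≈ (1.960 + 0.842) √(2(1 − rho²)/60), which is .338, .409 and .443 for rho = .75, .60 and .50. Exact F with 117 error df gives .34, .41 and .45.

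**The case against.** The strongest reply is that the fault may be a wrong symbol plus an input that a condensed article can leave out. With f = .10 in place of f-squared, and an epsilon of about .77 in four cells or .45 in two groups, the answer lands at about 160. This stands as a reason not to say that no calculation could give 160. It does not rescue the paragraph: it requires a different effect-size metric from the one printed, and the four-cell version treats a parent and child from one family as independent.

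Several stronger readings are tempting, and the document does not support them.
- **That the trial is underpowered.** At f-squared = .10 as printed, 160 exceeds every repeated-measures requirement above. The 23% figure needs both f = .10 and the condition main effect as target, and the paragraph says neither.
- **That the pilot effect is about ten times smaller than the planned one.** This holds only if the printed eta is literal. A lost superscript explains it as well, and then pilot and plan agree.
- **That the .75 was wrongly carried over from the one-month, self-report pilot.** The paragraph gives no source for it beyond the team's previous research.
- **That a null result would exclude no difference.** That is read from the confidence interval, not from the planning effect size.

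It can also be said that powering the four-time ANOVA matches the primary analysis as written. That is fair. The baseline-adjusted six-month figures above belong to a comparison that the protocol does not specify, so they supplement the power statement for the planned test and do not replace it.

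**Conclusion.** The point holds in limited form. The printed inputs give about 12 or 88 families for the 2 x 4 primary analysis and at most about 124 to 126 for the 2 x 2 x 4 variants. At f-squared = .10, 120 completers have 97% to more than 99.9% power, so 160 families at 80% power is not what the inputs deliver. If f = .10 was intended, the answer under sphericity is 94 or 854, and power with 120 completers is 97% or 23%. These results assume rho = .75 and 25% attrition, and sphericity except where an epsilon is given. The finding is an irreproducible figure with an unnamed target. It is not a demonstration of too few families. The eta in Pilot research and the f-squared in the sample-size paragraph cannot both be taken literally as the same effect, so one symbol has to be confirmed or corrected.

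**What to change.** Keep 160 families and rewrite the paragraph as follows.
1. Replace f-squared = .10 with the metric and value actually entered.
2. Name the powered test (condition x time or condition effect, in the 2 x 4 analysis on one child per family), with its epsilon and the numbers before and after attrition.
3. Restate the power or detectable effect for 120 completers. At correlation .75 and sphericity, 80% power corresponds to f of about .076 for condition x time or about .23 for the condition main effect.
4. Because the question is the six-month difference, also report what is detectable there. If adjusted for baseline, this is about .34 SD at correlation .75, .41 SD at .60 and .45 SD at .50. The baseline SD pooled over arms could turn this into activity units; Results reports 110 families with complete baseline measures.
5. In Pilot research, state whether .08 to .11 is eta or eta-squared.

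The cost is one reworded paragraph and one confirmed symbol. Enrolment, randomization and the planned analysis do not change. The downside is that the restated detectable effect may look less favourable than the present wording.

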### Hypotheses

We hypothesize that adherence will be higher for the planning condition in comparison to the more standard physical activity education condition. We also propose that the effect may wane over time from the initial measurement period but all outcomes will remain significantly higher at six months. We hypothesize that the planning condition will not affect intentions but will positively affect health related fitness and QOL. We also hypothesize that the covariance of the assigned conditions (planning, education) on use/adherence will be explained by planning and the use of behavioral regulation strategies (i.e., manipulation check). In turn, the covariance between planning and behavioral regulation strategies and health-related outcomes will be explained by physical activity adherence among conditions. In addition, affective attitude and perceived behavioral control will predict intention, intention will predict planning and planning will predict adherence across conditions. Finally, we hypothesize that children will show greater adherence to the planning condition than their parents. No differences in gender or season are hypothesized but these are exploratory research questions because there is limited research at present to make any definitive statement.

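### The claim that 160 families is ample for the physiological outcomes does not follow from the reason given; power for fitness and body composition is unknown

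*Protocol article*

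**What the plan says.** The section on statistical power and sample size sets the target on adherence to physical activity, the primary outcome: 160 families, "80 per group) will be recruited to detect a small-medium effect size" (printed as f² = .10), "with a type one error of .05", "an average correlation of .75 across time for our DV of interest" "and a power of .80", with 25% attrition allowed for.

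It then turns to the physiological outcomes, which are to be tested as a 2 (condition) x 2 (time) interaction. Two sentences carry the argument: "Physiological parameters have larger effect sizes than the social/psychological variables in the study due to smaller standard error scores", and then "The proposed sample size is, therefore, more than adequate to ensure sufficient statistical power for the physiological measurements".

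Two other places bear on this. The section on pilot research says that physical fitness was not assessed in the pilot. The hypotheses section sets out a chain in which condition acts on adherence through planning and regulation strategies, and the association of planning and regulation with "health-related outcomes will be explained by physical activity adherence among conditions".

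**The concern.** This is a stated inference, not something left for a fuller document. Its premise is that smaller standard errors make effects larger. A standardised effect is a mean difference divided by an SD. A standard error also depends on the number of participants and does not fix that ratio. If the phrase means error of measurement, the sentence still says nothing about the numerator: how far a workbook, a wall calendar and booster sessions shift strength, waist or skinfolds over six months.

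The stakes lie in how a null result is read. The pilot section presents fitness and quality of life as the check on whether behaviour change brings the health gains that justify promoting activity. If the fitness and body-composition comparisons come out null, a prior statement of ample power invites the conclusion that there is no health benefit. The documents do not support that reading.

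**Working it through.** **The plan's own figure.** There is none for the physiological outcomes: no effect size, SD, correlation or power. The 160 belongs to adherence. In the usual repeated-measures form for a 2 x 4 interaction it is not recovered from the stated inputs (f = .10 gives 70 completers, 94 recruited; f² = .10 gives 9 completers, 12 recruited). That is a separate question, and nothing below depends on it.

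**Inputs.** From the power section: 80 per arm and 25% attrition, so 80 x (1 − .25) = 60 completers per arm; alpha .05; power .80. The only correlation given is .75, and it is for adherence. Correlations of .90 and .95 for physiological measures are assumptions, used to show the range. One person per family is counted.

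**Detectable difference, 2 x 2 interaction.** In units of the between-person SD:

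- SE of the difference in change = √(2(1 − ρ)) × √(2/60)
- Detectable difference at 80% power = 2.83 × SE

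For six-month values adjusted for baseline, SE = √(1 − ρ²) × √(2/60).

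| ρ (baseline to six months) | SE, change | Detectable, 2 x 2 | SE, adjusted | Detectable, adjusted |
|---|---|---|---|---|
| .75 | .1291 | .365 (about .37) | .1208 | .342 (about .34) |
| .90 | .0816 | .231 (about .23) | .0796 | .225 |
| .95 | .0577 | .163 (about .16) | .0570 | .161 |

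The ratio of the two SEs is √((1 + ρ)/2) = .935, .975 and .987, so adjustment gains about 6%, 3% and 1%.

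**Does the primary margin carry over?** Use the noncentral F with λ = f² × N × m/(1 − ρ), N = 120 and ρ = .75. At f = .10, the 2 x 4 design (m = 4) has power .97. The 2 x 2 design (m = 2) has λ = .01 × 120 × 2/.25 = 9.6 and power .87. At the same f and ρ, the physiological comparison therefore has less power than the primary one.

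**How wide is the unknown?** Power of the 2 x 2 interaction at 120 completers, if the physiological effect is some fraction of the effect used for sizing (the fractions are assumptions):

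| Fraction of f = .10 | ρ = .5 | ρ = .75 | ρ = .90 |
|---|---|---|---|
| 100% (.40 SD difference in change) | .58 | .87 | .998 |
| 70% | .33 | .58 | .93 |
| 50% | .19 | .34 | .68 |
| 30% | .10 | .15 | .31 |

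If f² = .10 is taken literally (f = √.10 = .316), power is at least .93 down to half the effect, and .54, .83 and .996 at 30% of it. Power thus runs from about .10 to nearly 1, depending on inputs that the article does not give.

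**The mediation chain.** Under full linear mediation, the standardised effect on fitness is the effect on activity times a standardised path of at most 1. It is then no larger than the effect on activity measured without error.

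**The case against.** Four points on the other side deserve weight.

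*Reliability does help.* Measurement error inflates the observed SD, so observed d = true d × √reliability. A more reliably measured outcome shows a larger standardised effect for the same true shift. Read as error of measurement, the protocol's sentence has a real mechanism behind it. This stands. What is missing is any evidence that the mechanism outweighs a smaller true shift in fitness.

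*The hypotheses do not strictly contradict the claim.* The comparison in the power section is with social and psychological variables, not with accelerometer activity, and the article expects no effect on intentions. Fitness effects larger than some psychological ones would fit its own predictions. The tension is with planning and regulation, which sit upstream. It also needs full mediation and error-free activity: partial mediation, or a noisy activity measure that attenuates the observed activity effect, could reverse the ordering. This stands too.

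*A reader might infer that the trial is underpowered for fitness.* The documents do not support that. Low power figures require an assumed effect on activity and an assumed activity-to-fitness path, neither of which is given. At f = .10 and ρ = .75, power is about 87%, and a literal f² = .10 gives more.

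*Sixty per arm may understate the information.* Fitness is measured in parents and children. If one parent and one child were pooled and the pilot's parent-child correlation of .21 applied to these outcomes (an assumption), detectable differences would shrink by √((1 + .21)/2) = .78, to about .28, .18 and .13 SD.

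Finally, these are secondary outcomes, and neither the target of 160 nor the primary analysis rests on the two sentences.

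**Conclusion.** The concern holds as a point about an unsupported claim. The article asserts ample power for the physiological outcomes on a reason that does not establish it, with no physiological inputs and no pilot data on fitness. Its own causal chain gives no ground for expecting the larger effects and, under full mediation with error-free activity, would cap them at the effect on activity. Power is unknown, not shown to be low.

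What can be stated is the detectable difference: about .37, .23 or .16 SD at correlations of .75, .90 or .95. This rests on 60 completers per arm, one person per family, two-sided alpha .05 and assumed correlations. The primary sample size is unaffected.

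**What to change.** 1. Delete the two sentences on physiological effect sizes and adequacy.
2. Put in their place the detectable difference for the physiological outcomes at about 60 completers per arm, one person per family, with the assumed correlation declared (about .37, .23 and .16 SD for the 2 x 2 interaction at .75, .90 and .95). If parents and children are to be pooled, say so and state the within-family correlation used.
3. Report these outcomes with confidence intervals, and state that a null result will not be read as evidence of no benefit from an adequately powered test.
4. Analyse six-month values adjusted for baseline instead of the 2 x 2 condition-by-time interaction. The detectable difference falls from about .37 to .34 SD at a correlation of .75, with less gain at higher correlations.

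The cost is wording plus one change to a secondary analysis that uses data already being collected. No extra families or measurements are needed. A stated property of the design becomes less favourable.

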## Results

To date, we have obtained ethical approval, registered the trial and have 137 families recruited from the Greater Victoria region. Ethical approval was received from the University of Victoria Human Research Ethics Board. We aim to complete recruitment by December 2015. From the 137 families recruited, 110 have completed all of the baseline measures, 62 have completed the six-week measures, 50 have completed the three month measures, and 40 families have completed the study. The study is ongoing and data analysis will continue into 2016. Please see Fig. 1 for the study procedures and participant flow chart.

**Fig. 1 Fig1:**
[figure not shown]
Study Procedures and Participant Flow Diagram

## Discussion

This protocol describes the implementation of a randomized controlled trial that utilizes planning strategies to try and increase physical activity among families based on the assumptions of the M-PAC framework as a conceptual model. Research findings will be important to public health as they may help to determine if providing low-cost, scalable and evidence-based planning strategies for family physical activity can aid in producing higher adherence to physical activity.
